#### Interventions

##### Group support psychotherapy (GSP)

The content of the GSP has been described in previous publications (29, 30). GSP sessions for caregivers will proceed as previously described in the SEEK-GSP trial (20). GSP sessions for the young people will follow the same format but with a focus on challenges faced by young people living with HIV and will be delivered using play materials. Besides being gender specific, they will also be age specific with participants being grouped into the following age categories: 10–13; 14–16 and 17–18) GSP will be delivered in eight weekly sessions, each lasting 2–3 h. Participants will be divided into sex-specific groups of 10–12 participants. The groups will be closed-meaning that once the group is formed and therapy initiated no other participant can join the group. Trained health workers of the same sex as the group participants will deliver the intervention material following a scripted manual.

The first session addresses issues related to introductions, the group process, expectations, and ground rules and making a pledge to commit to all sessions. Simple games will be used to explain concepts and help the young people get to know each other's name.

The second session will use pictures and practical demonstrations with balloons, to explain the presentation and consequences of abnormal emotions such as persistent sadness, fear, anxiety and anger and how they relate to living with HIV. Thereafter, participants will be asked to communicate with peers and share newly learned knowledge.

In sessions three and four, group participants share their most painful experiences. Here, various techniques will be used to help the young people open up. For example, expressive art exercises of body pain and heart wound. Here the young people are asked to draw a figure of the human body and place a mark where they feel pain. The counselor then encourages them to talk about the feelings associated with the pain they feel in the body part that is hurting. Another technique is to present a timeline from childhood to present and ask the young people to place both positive and negative events on their time-line. Thereafter, participants are encouraged to share other problems with a trusted elder in their household or community. In sessions five and six, practical demonstrations of culturally positive coping skills such as the stress bucket, gardening, seed pounding and crocheting are used to teach participants positive coping skills. The last two sessions are dedicated to income-generating skills that young people can use to support their caregivers income generating projects. Our previous research revealed a need for an intervention that focused on treatment of depression symptoms and livelihood skills development to improve household basic income (29). Poverty is a potent risk factor for depression and researchers recommend mental health interventions that can alleviate poverty (31).

##### Standard of Care—Intensive Adherence Counseling

Both the World Health Organization (WHO) and the Ugandan ART guidelines recommend that asymptomatic persons living with HIV who have been identified with viral load (VL) ≥1,000 copies per ml should be offered Intensive Adherence Counseling (IAC) for 3–6 months (see Table 1) and repeat VL testing before switching to second-line therapy (32). Individuals with detectable viral load 6 months after initiating ART are invited to participate in IAC in the clinic, which consists of at least four sessions with an HIV care provider. Key messages in each counseling session are summarized below.

**Table 1 T1:** Intensive Adherence Counseling Guide

Guide	Components
**IAC Session 1**	
Assess	• Explain purpose of session º Disclose VL test results to client and explain the meaning of suppressed and non-suppressed VL º Explain reasons for non-suppressed VL results (non-adherence to drugs or drugs may not be working well) º Discuss implications of non-suppressed results to the client • Determine adherence levels º Calculate the adherence score using the adherence percentage formula • Assess client's barriers to adherence º Use the adherence assessment checklist to ascertain client's adherence practices. º Identify barriers to client's adherence (arising from the assessment)
Advise	• Identify information gaps from assessment º Educate client in relation to specific barriers identified • Review benefits of good adherence º Assess client's knowledge of benefits º Provide correct and complete information on • Discuss consequences of non-adherence º Assess client's knowledge on the dangers of non-adherence º Educate client on the consequences of non-adherence
Assist	• Evaluate the underlying causes of the identified barriers º Prioritize the barriers º Identify possible root causes of each barrier (where applicable) • Identify client specific strategies to overcome identified barriers º Discuss possible options to address key barriers º Provide information about available support systems e.g., CBOs, peer support groups etc • Discuss the pros and cons of each strategy/option
Agree on	• Agree on client's action points to address the key barriers º Identify appropriate strategies º Provide relevant and necessary information • Evaluate each action point using the 5 Ws and 1H º What, where, when, who, which, how? • Document agreed upon action points on the IAC session form • Develop and document a new adherence plan on the IAC session form
Arrange	• Summarize the session º Review the action points º Review the new adherence plan • Arrange for ART refill • Explain the schedule for IAC intervention º Explain the number of sessions º Emphasize appointment keeping • Schedule the 2nd IAC session • Document the next appointment date on the IAC session form • Remind client to bring remaining pills at next visit • Refer and link to other services as appropriate
**IAC Session 2**	
Assess	Assess adherence levels • Document the adherence score • Compare current score with the previous Assess progress in dealing with barriers • Identify what worked • Identify what did not work • Discuss new strategies Assess compliance to adherence plan • Identify what worked • Identify what did not work • Discuss new strategies Assess for possible new barriers to adherence • Use adherence assessment checklist
Advise	Do as in IAC Session 1
Assist	Do as in IAC Session 1
Agree on	Do as in IAC Session 1
Arrange	Do as in IAC Session 1
**IAC Session 3**	
Assess	Do as in IAC Session 2
Advise	Do as in IAC Session 1
Assist	Do as in IAC Session 1
Agree on	Do as in IAC Session 1
Arrange	Review Adherence Scores For 1st, 2nd And Current IAC Visits • If Adherence Score Is Consistently Good (>95%) For Three Consecutive IAC Visits, Give 1 month Appointment For 2nd VL Bleeding • If Adherence Score Is Not Consistently Good For Three Consecutive IAC Sessions, Give Appointment For 4th IAC Session Give Appointment For 2nd Bleeding For VL Test (After 1 Month) • Remind And Emphasize To Client To Keep The Next Appointment. • Flag The Client's File As Due For Repeat VL Testing (Indicate Due Date On The Red Sticker) Discuss Reminder Plans With Clients Who Are Due For Bleeding • Provide ARV Drugs For 1 Month (Strictly) • Call Client 1 Week To The Due Date To Remind Them Of Appointment

#### Participant safety

During baseline assessments, participants will be carefully screened and individuals for whom the interventions are deemed medically inappropriate or unsafe will be excluded as described in the exclusion criteria. Independent outcome assessors will screen all participants for adverse events at the end of treatment and at 6 months after the end of the intervention using a standard interview and reporting form.

Any unfavorable and unintended sign or symptom associated with the participation in group support psychotherapy, regardless of whether it is considered related to the therapy will be regarded as an adverse event (AE).Any AE that results in any of the following outcomes: Death, Life-threatening, Event requiring inpatient hospitalization, Persistent or significant disability/incapacity will be regarded as a serious adverse event (SAE). Expected AEs associated with this study would be suicide attempts due to lack of treatment response to the group support psychotherapy.

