#### Randomisation and masking

Randomisation will be done by urn randomisation picked by each participant. The young males and females will be separated into two groups. Each group will be presented with pieces of paper in opaque envelopes whereby half the number of papers will be marked X and the other half Y. Each member of the group will be asked to each pick one envelope. Individuals who pick papers with X will be assigned to both GSP and IAC while those who picked papers with Y will be assigned to IAC only. The same process was repeated for the caregivers.

By design, both experimental and control interventions will be identifiable to participants but will be masked to independent outcome assessors, and data analysts.

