##### AE management

During participant recruitment, individuals will receive a suicide risk assessment (33). Individuals with high suicide risk will be excluded from the study. Those with a low to moderate risk will be included, their thoughts will be assessed at every group meeting and care givers will be asked to keep close watch on the affected individual. If suicidal thoughts are still present after 4 sessions of GSP-IAC or IAC only these individuals will be referred to a mental health worker in the Kitgum Mental Health Clinic. Details of the trial risk management plan are provided as Supplementary material.

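### Adverse events, and so serious adverse events, are defined only in relation to group support psychotherapy, which leaves the IAC-only arm outside the written definition

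*Protocol article*

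**What the plan says.** Four statements under Participant safety in the protocol article matter here.

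- **Definition of an AE.** It is "Any unfavorable and unintended sign or symptom associated with the participation in group support psychotherapy", and the sentence continues: "regardless of whether it is considered related to the therapy will be regarded as an adverse event".
- **Definition of an SAE.** It is built on the first: "Any AE that results in any of the following outcomes", followed by a list that includes death and inpatient hospitalisation.
- **Expected events.** "Expected AEs associated with this study would be suicide attempts due to lack of treatment response to the group support psychotherapy".
- **Who is screened.** "Independent outcome assessors will screen all participants for adverse events at the end of treatment", and again six months after the intervention ends, on a standard interview and reporting form.

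The subsection AE management plans for both arms. Its referral rule begins: "If suicidal thoughts are still present after 4 sessions of GSP-IAC or IAC only". It also refers the reader to a supplementary risk management plan, which is not among the documents.

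Under Study design, the control arm receives IAC only. It has no GSP sessions.

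**The concern.** The safety question in this trial is comparative: does adding GSP to IAC cause harm? The question is a real one. In the third and fourth sessions, young people are asked to share their most painful experiences, and those at low to moderate suicide risk are enrolled. Suicide attempts or admissions in the GSP arm can be interpreted only against the number in the IAC-only arm, counted under the same rule.

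The written rule does not provide that. It ties an AE to taking part in GSP, which only one arm does. If it were followed, the same event would count in one arm and not in the other. The Introduction says that the pilot's data will be used to design a definitive cluster randomised trial, so a one-sided definition could be carried forward.

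**Working it through.** The plan gives no figure to reproduce, so the check sets the statements side by side.

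**Step 1. Who takes part in GSP.** Study design randomises 120 dyads 1:1 to GSP plus IAC or to IAC alone. No IAC-only participant takes part in GSP.

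**Step 2. What the AE sentence requires.** It has two parts. The first sets a condition, association with taking part in GSP. The second waives any judgement of causality. Waiving causality does not waive the first condition: there must still be participation in GSP for the event to be associated with. An IAC-only participant cannot meet it.

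**Step 3. What follows for SAEs.** An SAE must first be an AE. An event that fails Step 2 cannot be an SAE, however grave its outcome.

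**Step 4. What follows for the expected AE.** The only one named is a suicide attempt attributed to non-response to GSP. That cannot arise in a participant who was never offered GSP.

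**Step 5. The literal result by arm.**

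| Event | GSP plus IAC | IAC only |
|---|---|---|
| Unfavourable symptom during the trial | AE | Not an AE |
| Hospital admission or death | AE and SAE | Neither |
| Suicide attempt after non-response | Expected AE | Neither an AE nor an expected AE |

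**Step 6. Whether other text corrects it.** Screening covers all participants, and the referral rule for persisting suicidal thoughts names both arms. Both suggest that the authors meant to cover both arms. Neither redefines an AE or an SAE, and nothing else in the article does.

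**Step 7. Size.** As planned, 60/120 = 50.0% of the young people fall outside the definition. The Trial status section gives arms of 61 and 60 beside a stated total of 120; on those arm sizes the share is 60/(61 + 60) = 60/121 = 49.6%. If caregivers are also counted as participants, the number of people doubles and the share stays at about half. This share only reflects 1:1 allocation. The documents give no event rate, so the number of affected events cannot be estimated.

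**The case against.** The strongest reply is that the procedures already cover both arms. Everyone is screened on a standard form, suicidality is managed in both arms, and Table 2 schedules the suicide-risk scale at 0, 2, 6 and 12 months with no restriction by arm. On this view the sentence is loose drafting, and IAC-only events were probably recorded anyway. In addition, this is a condensed article, and the risk management plan or the AE form could carry an arm-neutral definition. AEs are not listed as an outcome in Table 2, and the article states no between-arm AE analysis.

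Much of this stands. It makes lost data unlikely and a drafting error the best explanation. It does not remove the problem of classification: either recorded IAC-only events are left out under the written rule, or the reported counts follow a rule that is not the written one. Nor is this detail left to another document, because the article states a definition and that definition does not fit a two-arm trial.

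Two stronger readings are tempting and are not supported.

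- A reader might infer that assessors cannot apply the definition, because allocation "will be masked to independent outcome assessors, and data analysts". The article gives assessors the task of screening. It does not say that they classify events as AEs or SAEs, so no conflict with masking is shown.
- A reader might infer that suicidality is monitored at different times in the two arms, because "their thoughts will be assessed at every group meeting" and the referral trigger counts sessions. That is a separate matter from the AE definition. It depends on how IAC sessions were timed, which the article does not give, and the risk management plan may deal with it.

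**Conclusion.** The point holds as a defect in a stated definition. Read literally, events in the IAC-only arm, about half of the young people, are neither AEs nor SAEs, and the resulting counts would not compare the arms on equal terms.

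This conclusion rests on the article's wording alone and assumes that no unseen document overrides it. If the risk management plan or the AE form already uses an arm-neutral definition, what remains is a correction to the published text. No stated efficacy analysis is affected.

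A reader might also infer that IAC-only events went unrecorded. The documents do not support that, because screening was planned for every participant.

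**What to change.** 1. Define an AE as any untoward sign, symptom or event after randomisation in either arm, whether or not it is thought related to an intervention. The SAE definition then needs no change of its own.
2. Reword the expected-AE sentence so that it covers suicide attempts in either arm, without reference to response to GSP.
3. Recruitment has closed, so for this trial classify the AE forms from the two scheduled screenings (at the end of treatment and six months later) under that rule, masked to arm. Report AEs and SAEs by arm.
4. Use the same wording in the definitive trial's protocol. If the risk management plan or AE form already has it, say so and cite it.

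The cost is minor re-classification work and one table by arm, with no new visits or data collection. The limit is that re-classification cannot recover IAC-only events that were not recorded at the time. If there are signs of that, the report should say so beside the table.

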## Methods

### Study setting

Study participants will be recruited from community based HIV clinics in Kitgum district. The clinics take care of approximately 500 young people aged 18 years and below living with HIV. At the time we conceptualized this study, HIV clinic registers in Kitgum district showed that 60% of young people living with HIV (PLWH) initiated on ART were not suppressing the HIV virus. Therefore, we drew our study sample from a pool of approximately 300 young PLWH who had viral non-suppression. Kitgum district has a population of 232,000 individuals with over 90% engaged in small scale agriculture and animal husbandry as their major income generating activity. Kitgum district endured a brutal civil war for two decades (1987–2007) which led to a breakdown of health care delivery systems, loss of property and infrastructure.

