**Secondary outcomes**					
Fidelity	A semi-structured self-administered questionnaire completed by group facilitators will assess whether or not the interventions were delivered as planned.		✓		
Contextual influences	A semi-structured self-administered questionnaire completed by group facilitators will assess any facilitators or barriers to intervention delivery that they observed during group sessions.		✓		
Depression symptoms	The 25-item revised child and adolescent anxiety and depression scale (RCADS-25) will be used to assess anxiety and depression symptoms. Although it has not been validated in Ugandan populations, its items have face validity. It has been widely used in Europe North and South America with internal reliability ranging from 0.87 to 0.90 (35, 36), a high sensitivity of 90% and specificity of 75% (37). RCADS scores will be modeled as a continuous variable.	✓	✓	✓	✓
Suicide risk	Suicide risk will be assessed using the 10-item Patterson suicide risk assessment tool. Its validity and reliability have not been evaluated in Uganda. Due to its brevity and face validity it has been used in both adults and young people in Uganda (33)	✓	✓	✓	✓
Post-traumatic stress symptoms	The 17-item Clinician-administered post-traumatic stress disorder scale for children and adolescents (CAPS-CA) will be used to assess PTSD symptoms. Although it has not been validated in Ugandan populations, its items have face validity The tool has been widely used in Europe North and South America with internal reliability ranging from 0.83 to 0.87 (38–41), a high sensitivity of 90% and specificity of 75%. CAPS-CA scores will be modeled as a continuous variable.	✓	✓	✓	✓
Social support	The child and adolescent social support scale (CASS) will be used to assess social support. Although it has not been validated in Ugandan populations, its items have face validity. It's internal consistency reliability coefficient ranges from 0.87 to 0.94) in studies conducted in Europe (41).	✓	✓	✓	✓
Stigma	The 8-item HIV stigma scale for children (HSSC-8) will be used to assess stigma. It has internal consistency reliability coefficient of 0.81 (42).	✓	✓	✓	✓

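### The safety definitions grade suicide attempts by four outcomes only, tie expected attempts to non-response to GSP, and do not fit the IAC-only arm

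*Protocol article*

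**What the plan says.** All the definitions at issue are in the Participant safety section of the protocol article.

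- **Adverse event:** "Any unfavorable and unintended sign or symptom associated with the participation in group support psychotherapy, regardless of whether it is considered related to the therapy" is to be regarded as an AE.
- **Serious adverse event:** "Any AE that results in any of the following outcomes: Death, Life-threatening, Event requiring inpatient hospitalization, Persistent or significant disability/incapacity" is the full list. It has no criterion for an event that matters in itself, and it does not name suicide attempts.
- **Expected events:** "Expected AEs associated with this study would be suicide attempts due to lack of treatment response to the group support psychotherapy". No other event is named as expected.
- **Ascertainment:** "Independent outcome assessors will screen all participants for adverse events at the end of treatment and at 6 months after the end of the intervention". The assessors work from a set interview and form.

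The AE management section adds that people at high suicide risk are excluded and that those at low to moderate risk are enrolled and monitored. Its referral rule covers both arms: "If suicidal thoughts are still present after 4 sessions of GSP-IAC or IAC only these individuals will be referred". It points to a supplementary risk management plan, which is not among the documents at hand. Suicide risk is also a secondary measure in Table 2: "Suicide risk will be assessed using the 10-item Patterson suicide risk assessment tool", at 0, 2, 6 and 12 months.

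**The concern.** The trial enrols 10 to 18 year olds, some with known low to moderate suicide risk, and names one harm that it expects. The grading, attribution and arm coverage of that harm should therefore be clear. The section falls short on each.

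- **Grading.** Seriousness depends only on how the attempt ended, so some attempts will not reach the SAE table.
- **Attribution.** The expected-event sentence explains attempts as the therapy failing to help. A possible harm of the therapy could then be read as absence of benefit.
- **Comparison between arms.** The AE definition refers to one arm's treatment. If staff applied it as written, events in the other arm would have no category, and AE counts by arm would not be comparable.

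At stake is what the pilot can say about harm, and what safety definitions the planned definitive cluster randomised trial inherits from it.

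**Working it through.** The article states no expected number of attempts, no SAE rate and no safety threshold, so there is no figure to reproduce. The check is to run four kinds of suicide attempt through the definitions as written.

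1. **GSP arm, at least one of the four outcomes met.** The event is an AE and an SAE. The definitions work.
2. **GSP arm, none of the four outcomes met.** The event is an AE, because the AE definition asks for no threshold of severity. It is not an SAE, because the list is closed and an attempt is not on it. It appears in the AE record and not in the SAE count.
3. **GSP arm, possibly provoked by the therapy.** The manual contains emotionally demanding material: "In sessions three and four, group participants share their most painful experiences". Whether such material could provoke an attempt is a hypothesis, and the article gives no evidence either way. The event is still an AE, since relatedness is disregarded. But the expected-event sentence does not describe it, because that sentence expects attempts only through non-response. Two statements in one section therefore treat cause differently: the AE definition leaves it open and the expected-event sentence fixes it.
4. **IAC-only arm, any outcome.** The participant is screened, because screening covers everyone. Read literally, the event is not an AE, because it is not associated with taking part in GSP. SAEs are a subset of AEs, so it cannot be an SAE either, even if fatal. The causal clause cannot apply, since this participant received no GSP to which they could fail to respond.

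Case 4 reaches furthest. The planned allocation is 60 per arm, so the literal AE definition has no place for events in 60/120 = 50% of the randomised young people. This cannot be the intention, because the screening sentence and the referral rule both cover the two arms. The definition and those two sentences need to be reconciled.

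The size of case 2 cannot be calculated. It would need the number of attempts and the share that meet none of the four outcomes, and the article gives neither.

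**The case against.** Several points on the other side are sound.

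- **Attempts are recorded either way.** A reader might infer that attempts are left out or under-counted. The article does not support that. Grading changes the label, not whether the event is collected, and an attempt that is fatal, life-threatening, disabling or requires hospitalisation is already an SAE. What stands is narrower: some attempts would be absent from the SAE count.
- **Access to a ward.** A reader might also argue that attempts escape the SAE rule because local care is poor, citing the Study setting remark that the war "led to a breakdown of health care delivery systems". That war is dated 1987–2007, and recruitment ran from June to October 2021. The SAE criterion speaks of an event requiring hospitalisation, which can be read as need rather than actual admission. The article also mentions a mental health clinic and a general hospital in Kitgum. This argument should not be used.
- **The expected-event sentence is not an attribution rule.** True: nothing says that other attempts are to be filed as lack of benefit. The clause still conflicts with the AE definition beside it and still cannot apply to the control arm.
- **Treating every attempt as serious is a grading choice.** Also true. The article does not contradict itself on that point, so a table of all attempts by arm would be an acceptable alternative.
- **The risk management plan is not shown.** It may deal with attempts and relatedness, and its content cannot be called missing. But the article states these definitions outright. If the plan differs, the two disagree and need reconciling.
- **It is late.** Recruitment has closed and analysis is in progress, so any change is retrospective. That calls for disclosure, and does not remove the reason for the change.

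**Conclusion.** The point holds in limited form, as a matter of wording and classification that should be corrected. As written, an attempt meeting none of the four outcomes is a non-serious AE and does not enter the SAE count. The expected-event sentence assigns a cause that conflicts with the relatedness-neutral AE definition and cannot accommodate an attempt provoked by GSP or one in the IAC-only arm. The AE definition, read literally, does not cover the IAC-only arm although that arm is screened.

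No numerical effect can be given. The documents contain no attempt rate and no admission rate, so any percentage would be invented. The conclusion rests on reading the published definitions as operative. If the supplementary plan or the reporting form already applies one definition to both arms, the practical effect is smaller and what remains is to correct the article's text. The documents also do not show that the pilot will declare GSP safe: safety is not among its stated objectives.

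**What to change.** Change the Participant safety section as follows.

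1. State that AEs and SAEs are defined identically in both arms, by replacing the link to GSP participation with a link to participation in the trial.
2. Record any suicide attempt in either arm as an SAE. At the least, tabulate all attempts by arm whatever their seriousness.
3. Delete the clause giving non-response to GSP as the cause of expected attempts, so that relatedness is judged case by case.
4. Check the result against the supplementary risk management plan and make the two agree.

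Because data collection is far advanced, apply the revised rule to the completed AE forms before the safety table is made, and report it openly as a post hoc reclassification. These changes concern recording and reporting only, not the care of participants.

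The cost is a few wording changes and a re-read of completed forms. The downside is a somewhat higher SAE count and a few more reports to the ethics committee.
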